## Abstract

**Introduction:** Mental disorders are a leading cause of disability worldwide. Depression has a significant impact in the field of occupational health because it is particularly prevalent during working age. On the other hand, there are a growing number of studies on the relationship between “well-being” and employee productivity. To promote healthy and productive workplaces, this study aims to develop a technique to quantify stress and well-being in a way that does not disturb the workplace.

**Methods and analysis:** This is a single-arm prospective observational study. The target population is adult (>20 years old) workers at companies that often engage in desk work; specifically, a person who sits in front of a computer for at least half their work hours. The following data will be collected: (a) participants' background characteristics; (b) participants' biological data during the 4-week observation period using sensing devices such as a camera built into the computer (pulse wave data extracted from the facial video images), a microphone built into their work computer (voice data), and a wristband-type wearable device (electrodermal activity data, body motion data, and body temperature); (c) stress, well-being, and depression rating scale assessment data. The analysis workflow is as follows: (1) primary analysis, comprised of using software to digitalize participants' vital information; (2) secondary analysis, comprised of examining the relationship between the quantified vital data from (1), stress, well-being, and depression; (3) tertiary analysis, comprised of generating machine learning algorithms to estimate stress, well-being, and degree of depression in relation to each set of vital data as well as multimodal vital data.

**Discussion:** This study will evaluate digital phenotype regarding stress and well-being of white-collar workers over a 4-week period using persistently obtainable biomarkers such as heart rate, acoustic characteristics, body motion, and electrodermal activity. Eventually, this study will lead to the development of a machine learning algorithm to determine people's optimal levels of stress and well-being.

**Ethics and dissemination:** Collected data and study results will be disseminated widely through conference presentations, journal publications, and/or mass media. The summarized results of our overall analysis will be supplied to participants.

**Registration:** UMIN000036814

## Introduction

Mental disorders are a leading cause of disability worldwide and, among mental disorders, major depressive disorder was ranked number 1 in years lived with disability in 2017 (1). The lifetime prevalence of depression in Japan is estimated at 6.2% (2002–2006 estimate), which makes it the country's most common mental illness (2). The disease costs are also enormous and are estimated to exceed 3.09 trillion Japanese Yen (~30 billion U.S. dollars) per year (3). Depression has a significant impact in the field of occupational health because it is particularly prevalent during working age (20–65 years of age). It is estimated that more than half of the social loss due to depression is attributed to loss of labor productivity through absenteeism and presenteeism (2). The Japanese government has implemented measures against long working hours (Standards on limits of overtime work in 1998; the revision of the Industrial Safety and Health Act in 2006) and has introduced the stress check system (enforced as of December 2015), but there has not been a significant impact from those measures. In fact, the number of workers' compensation claims related to mental disorders are increasing each year.

On the other hand, there are a growing number of studies on the relationship between “well-being” and employee productivity. The happiness of employees has been reported to be associated with creativity and productivity (4). As the birthrate continues to decline and the aging population continues to increase in Japan, the working age population is also decreasing, requiring each employee to make the most of his/her abilities. Therefore, preventing negative factors such as depression and promoting well-being are major challenges for health management in the workplace and ensuring a stable economy.

Conventionally, it is known that heart rate variability (HRV) reflects autonomic nerve activity and serves as an index of psychological and physical stress. There are many suggested indicators for stress, including standard deviation of all normal-to-normal R-R intervals (SDNN) and the percentage of successive R-R intervals that differ by >50 ms (pNN50) with time domain variables and low frequency (LF), high frequency (HF), and their ratio (LF/HF) as frequency domain variables (5).

In addition, techniques for estimating emotions and depressive symptoms have been developed based on the analysis of speech including formant frequencies (6). The autonomic nervous system and voice characteristics are closely related to each other because most of the vocal fold movement is stimulated by the recurrent nerve, which branches off from the vagus nerve. Johannes et al. reported that speech fundamental frequency increased with psychological load while there was no significant difference with physical load, suggesting that speech fundamental frequency is a good indicator of psychological stress (7). Nakatsu et al. reported that combination of linear prediction cepstral coefficients and pitch-related characteristics predicted classification of 8 emotions using artificial neural network (8).

Furthermore, electrodermal activity measured by a wearable device can reflect the activity of eccrine sweat glands that are controlled only by sympathetic nerve activity, and is therefore expected to be a stress indicator (9). Previous studies have used the above mentioned approaches to measure subjects' degree of stress; however, this prior research comprises only feasibility studies that have simply verified device performance, and/or studies with only a small number of patients or healthy individuals (10, 11).

Moreover, such approaches are only used to evaluate the so-called “short-term stress” of the study period, and are not necessarily reflective of the effects of medium- to long-term stress. In a workplace environment, it is expected that regardless of whether employees experience temporary stress, there should also be situations where people feel a sense of freedom and accomplishment when a task is completed or a problem overcome. To date, very few studies have revealed the relationship between vital data and mid- to long-term stress and well-being in the workplace (12).

With the development of information and communication technology, similar approaches trying to utilize such biological and/or behavioral data to identify depression are reported recently. For example, in the case of HRV, Dell'Acqua et al. reported that HRV reduction can be the predictor for depression as HRV of individuals with dysphoria and in those with past depression was lower than controls (13). Kemp et al. in their meta-analysis on HRV and antidepressant treatment, reported that depression was associated with reduced HRV, which decreased with increasing depression severity (14).

We have reported that the timing related speech features can reflect the severity of depression. Speech rate, pause time, and response time showed significant associations with the total score of Hamilton Depression Rating Scale (15, 16). We have also reported that body movement captured by infrared sensor can be reflective of depression severity (15, 17).

Not only using single modality but combining multimodal data and with machine learning approach it may be more realistic to screen depression or to predict severity of depression. Utilizing wrist band-type wearable device that record three-axis acceleration, heart rate, body temperature, and ultraviolet light exposure, we have reported that it was possible to identify patients with depression with an accuracy of 0.76, and to predict depression severity with a 0.61 correlation coefficient with Hamilton Depression Rating Scale score (15, 18).

This study, which is funded by the Japan Agency for Medical Research and Development (AMED), is an industry-academia collaborative research project that aims to develop new techniques for evaluating mid- to long-term stress and well-being using technologies that will not obstruct normal work environments. By doing so, we hope to promote healthy workplaces and, in the end, to prevent depression in the prime of life.

### Research Objectives

The general aim of this study is to develop a technique to quantify stress and well-being in a way that does not disturb the workplace. Our specific objectives are: (1) To evaluate the relationship between the obtained questionnaire-based stress and well-being scores and the employees' vital data, which are collected using: a technique for extracting pulse waves from an image captured by a camera attached to the employee's computer, a technique for extracting emotional components from speech, and a technique for measuring electrodermal activity using a wristband-type wearable device; and (2) to gather information regarding how and when employees are coping to reduce stress or promote enhanced well-being by comparing questionnaire-based stress and well-being scores and the employees' vital data.

## Methods and Analysis

### Study Design

This is a single-arm prospective observational study.

### Participant Criteria

#### Inclusion Criteria

Adult (>20 years old) workers at companies that often engage in desk work; specifically, a person who sits in front of a computer for at least half their work hours (3.5 h a day or more).

#### Exclusion Criteria

People who correspond to any of the following groups are excluded from this study:

(1) People currently receiving treatment for mental illness, such as depression;(2) People who suffer from diseases that may affect the acquisition of biometric information. For example, those who have a disease or disorder that affects pulse wave data measurement (persons who have paralysis or involuntary movements on their faces, or heart disease), those who have a disease or disorder that affects speech data measurement (speech difficulty caused by vocal cord extraction, etc.), or those who have a disease or disorder that affects measurement with wearable devices (persons with paralysis of the extremities or involuntary movement, etc.);(3) People who have difficulty operating a computer, such as using email or the internet;(4) People who cannot offer biometric information to researchers due to business/security reasons.

### Participant and Public Involvement

This study was supported by AMED at the stage of developing proof of concept for quantification of stress and well-being using pulse, speech, body motion, and electrodermal data. The study design was made by industrial doctors who served as consultants for some of the companies for which the participants of this study work. These industrial doctors, who are members of our research team, conducted preliminary meetings with the participants, and based on those meetings, they arrived at the question this study hopes to answer: whether stress and well-being can be quantified by pulse, speech, and electrodermal data. The results of this study will be made available to participants through debriefing sessions at each participating company.

### Data Collection

Data will be collected according to the observation period schedule in Table 1.

**Table 1 T1:** Schedule for data collection and evaluations during the study's observation period.

**Data collection**		**At the beginning**	**At the mid-point (2 weeks)**	**At the end (4 weeks)**
(A) Collection of background factors	Background characteristics (sex, age, department, work content, duration of service, etc.) Past stress check data, etc.	✓	If participant's environment changes, data will be updated.	
(B) Collection of data using external sensors	Pulse wave, speech, electrodermal activity, etc.	Acquired during business hours		
(C) Stress, well-being, and depression assessment using rating scale; self-reported daily condition	New occupational stress simple questionnaire (revised version): Estimated completion time, 5 min	✓	If participant's environment changes, data will be updated.	
	Perceived Stress Scale (PSS): Estimated completion time, 1 min			✓
	Satisfaction With Life Scale (SWLS): Estimated completion time, 1 min			✓
	Japanese version of Positive and Negative Affect Schedule (PANAS): estimated completion time, 1 min		✓	✓
	Japanese version of Flourishing Scale (FS-J): Estimated completion time, 1 min			✓
	Subjective well-being/ideal happiness: estimated completion time, 1 min			
	Japanese version of Patient Health Questionnaire-9 (PHQ-9): estimated completion time, 1 min			
	Self-reported daily condition: estimated completion time, 1 min	Daily at the end of work (not required)		

(A) Collection of background factors

After obtaining written consent, the following information will be obtained from each participant:

(1) Sex, age, job department, job content, duration of service, position/title, family composition, work commute, household income, etc.;(2) Information on past medical checkups and stress check information (with consent of participant);(3) Any current illnesses and prescriptions.

(B) Collection of biological data with sensing devices

Biological information will be recorded at participants' workplaces during the 4-week observation period using methods B-1 through B-3, as described below:

(B-1) Pulse wave data

Participants install software on their work computers that uses a camera built into or connected to the computer to record video images of the participant; the pulse wave data is extracted from the facial video images. The pulse wave data is automatically sent to cloud storage through the software. Participants are asked to start the software when they arrive for work; the software must also be restarted if the participant's computer is put into sleep mode. This contactless pulse wave sensing system has a strong correlation in the R-R interval values compared to data obtained using ECG (*r*^2^ = 0.978, *p* < 0.00001) (19).

(B-2) Voice data

Participants install software on their work computers that uses a microphone built into or connected to their work computer to record the emotional components (pitch, speed, etc.) of participants' speech data. The emotional component data is automatically sent to cloud storage through the software. Participants are asked to start the software when they arrive for work; the software must also be restarted if the participant's computer is put into sleep mode.

(B-3) Electrodermal activity data, body motion data, and body temperature

Participants are asked to wear the Embrace2 wristband-type wearable device, made by Empatica, Inc., continuously during work hours. The device is equipped with an electrodermameter, accelerometer, gyroscope, and thermometer (20, 21).

(C) Collection of stress, well-being, and depression rating scale assessment data; self-reported daily condition

Researchers will send participants an email with a unique URL link for a unique website where participants can answer questionnaires on stress and well-being online. The evaluation scales and their estimated completion times are as follows (see Table 1 for the evaluation schedule):

New Occupational Stress Questionnaire (modified version) (22)Perceived Stress Scale (PSS) (23)Satisfaction With Life Scale (SWLS) (24)Japanese version of Positive and Negative Affect Schedule (PANAS) (25)Japanese Flourishing Scale (FS-J) (26)Subjective Well-being/Ideal Happiness (27, 28)Japanese version of Patient Health Questionnaire-9 (PHQ-9) (29)Self-reported daily condition: an email with a unique URL will be sent to participants every business day; participants will input their condition (stress level, emotions, etc.) and sleep quality for the day in Likert scales, and include any special notes in 1–2 sentences (e.g., “I had a tough day,” “I was praised by my boss today,” etc.).

### Data Storage

The data of background factors (Data A) will be recorded on paper by the researcher and then entered by the researcher into the password-locked computer in the laboratory of the researcher and stored.

Pulse wave and voice data (Data B-1 and B-2) will be quantified and automatically uploaded to the server used by the researcher team through a Secure Sockets Layer (SSL) connection. The research team will download this data via an SSL connection to a research computer in the laboratory and analyzes it.

Data of electrodermal activity, body motion, and body temperature (Data B-3) will be captured by the wearable device and transferred to Empatica's cloud in encrypted form using proprietary software, where the raw data from the device will be analyzed and transformed into skin potential, heart rate, body movement, and temperature data. These sensing data will be eventually downloaded to the computers of the Keio University research team for analysis via an SSL connection.

The web-input data (Data C) such as stress, well-being, depression rating scale assessment data, and self-reported daily condition will be entered directly by participants by accessing an input format on a secure cloud computing service created by the research team. The entered data will be stored on the cloud, and the research team will access the cloud and downloads them to the laboratory's computer through an SSL connection.

All data above will be not accessible by the participants' employers.

### Data Analysis

The analysis workflow is as follows: (1) primary analysis, comprised of using software to digitalize participants' vital information; (2) secondary analysis, comprised of examining the relationship between the quantified vital data from (1), stress, well-being, and depression; (3) tertiary analysis, comprised of generating machine learning algorithms to estimate stress, well-being, and degree of depression in relation to each set of vital data as well as multimodal vital data. The primary analysis is conducted with technology already established by Panasonic and NEC, who are industrial collaborators in this study. In this research, the results of the primary analysis are used to generate machine learning algorithms for the secondary and tertiary analyses.

### Primary Analysis

#### Primary Analysis of Pulse Wave Data

Software from Panasonic installed on participants' work computers uses a camera to capture facial images of participants using facial detection. Based on skin color changes from blood flow in the images, the software extracts pulse wave data for the participant. The pulse wave data will then be clarified using filtering and noise removal techniques. SDNN, root mean square of successive differences in R-R intervals (RMSSD), Lorentz plot (Longitudinal axis/Transverse axis value), LH/HF ratio, and Tone-Entropy are calculated from the facial video images (1/30 s unit).

#### Primary Analysis of Voice

Software from Panasonic installed on participants' work computers uses a microphone to acquire speech data from participants. From this data, voice activity detection (VAD; presence/absence of voice), power (volume of speech), pitch, tension (strength of speech), and speech rate data are extracted (in units of 0.5 s), and an emotion estimate is calculated based on the results.

#### Primary Analysis of Electrodermal Activity

The Embrace2 wristband-type wearable device from Empatica, Inc., is equipped with an electrodermameter, accelerometer, gyroscope, and thermometer, which are used to record and analyze electrodermal activity, acceleration, angular velocity, and skin temperature.

### Secondary Analysis

Each result from the primary analyses of pulse wave, speech, and electrodermal activity data will be compared with the self-assessment results for stress, well-being, and depression. Then, we will determine the relationships between the vital data, stress, well-being, and depression. For example, such an investigation could be done by comparing the stress and well-being score quartiles with the vital data, or comparing them among subjects grouped according to depression symptom severity. Multiple regression analysis will be performed in order to predict stress, well-being, or depression using various kinds of vital data. Moreover, cluster analysis will be performed to find a group of people that have similar digital phenotypes and to seek for the potential relationships with clinical phenotypes.

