### Tertiary Analysis

We will attempt to build a machine learning model to predict depression, stress, or well-being based on single modalities. Various methods, such as support vector machine, decision tree, and deep learning, are used for the machine learning analysis. Machine learning algorithms that estimate stress, well-being, and degree of depression are generated from each of these vital data sets. We will attempt to build a model not only for single modalities, but also one that can utilize all the modalities, namely pulse wave data, voice data, electrodermal activity data, body motion data, and body temperature data, together.

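### Sensor features are the only named inputs to the regressions and machine-learning models, and the background data collected have no stated role in the analysis

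*Protocol article*

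**What the plan says.** All places are in the protocol article.

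- **Research Objectives**, first objective: "To evaluate the relationship between the obtained questionnaire-based stress and well-being scores and the employees' vital data".
- **Secondary Analysis**, regression: "Multiple regression analysis will be performed in order to predict stress, well-being, or depression using various kinds of vital data". Group comparisons are offered as an illustration: "For example, such an investigation could be done by comparing the stress and well-being score quartiles with the vital data", or across groups defined by severity of depressive symptoms. Neither adjustment nor stratification is mentioned.
- **Tertiary Analysis**: models are built first on single modalities and then on all of them, "namely pulse wave data, voice data, electrodermal activity data, body motion data, and body temperature data, together". No background factor is on that list.
- **Data Collection**, part (A), records for each participant "Sex, age, job department, job content, duration of service, position/title, family composition, work commute, household income, etc", then "Information on past medical checkups and stress check information (with consent of participant"), and "Any current illnesses and prescriptions". No later section uses these items in an analysis.
- **Sample Size** gives the only performance criterion: a root mean square error (RMSE) of 2 or less on the Perceived Stress Scale (PSS, range 0–40). No reference model is set beside it.

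**The concern.** Objective 1 is about association as well as prediction. If a background factor is related both to a sensor feature and to a questionnaire score, the two will correlate even when the feature carries no information of its own about stress or well-being. Sex with voice pitch, age with heart rate variability, and medication with heart rate variability or electrodermal activity are plausible routes, and the planned features include pitch (Primary Analysis of Voice) and several heart-rate-variability measures (Primary Analysis of Pulse Wave Data). An unadjusted result cannot be told apart from such a by-product.

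The models raise a second question. The study wants to quantify stress and well-being by unobtrusive sensing. A sensor-only error, however small, does not say how much of it could have been achieved from age, sex and job alone. The data for that comparison are in hand, but the comparison is not described.

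**Working it through.** **1. The plan's own figures.** The RMSE target is 5% × 40 = 2, as stated. Recruitment: 200 / (1 − 0.30) = 286 and 200 / (1 − 0.35) = 308, so the stated 300 lies within the range. The 200 is read from a pilot learning curve (Figure 1, not shown) and cannot be recomputed. None of these figures bears on confounding, and the fix changes none of them.

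**2. Correlation produced by a background factor.** Let r1 be the correlation of the factor with the sensor feature and r2 its correlation with the score. With no direct link between feature and score, the unadjusted correlation is r = r1 × r2. The documents give neither r1 nor r2, nor any significance level. All values below are assumptions.

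Probability of a significant result at n = 200, two-sided 5%, by Fisher z: with z = atanh(r) × √(200 − 3) = atanh(r) × 14.04, the probability is Φ(z − 1.96) + Φ(−z − 1.96).

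| Assumed case | r1 | r2 | r | Declared significant |
|---|---|---|---|---|
| Weak links | 0.1 | 0.1 | 0.01 | 5% |
| Sex and pitch, weak link to PSS | 0.8–0.9 | 0.05 | 0.04–0.045 | 9–10% |
| Age and heart rate variability (signs dropped) | 0.4–0.5 | 0.2–0.3 | 0.08–0.15 | 20–56% |
| Sex and pitch, moderate link to PSS | 0.8–0.9 | 0.15–0.20 | 0.12–0.18 | 39–72% |

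Worked example: r = 0.9 × 0.20 = 0.18; atanh(0.18) = 0.182; z = 0.182 × 14.04 = 2.55; Φ(0.59) + Φ(−4.51) = 0.72.

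These are single-feature correlations. They illustrate the mechanism and are not a forecast for the multiple regression.

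**3. What sensing adds.** Let the sensor correlate 0.3 with the score (R² = 0.09 alone), the background data correlate b with the score, and sensor and background correlate c with each other. The gain in R² over background is (0.3 − b × c)² / (1 − c²).

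- c = 0, any b: gain 0.09.
- b = 0.4, c = 0.4: (0.3 − 0.16)² / 0.84 = 0.0196 / 0.84 = 0.023.
- b = 0.7, c = 0.4: (0.3 − 0.28)² / 0.84 = 0.0004 / 0.84 = 0.0005.

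A sensor-only analysis reports 0.09 in all three cases.

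**4. Would a model that only recognises sex pass the RMSE target?** A predictor with correlation r has RMSE = SD × √(1 − r²). For r = 0.12 to 0.18 the factor is 0.993 to 0.984. The documents give no SD for the PSS. Assuming 5 to 8, the RMSE is about 4.9 to 7.9. Reaching 2 would need r = √(1 − 4/SD²), that is 0.92 (SD 5) to 0.97 (SD 8). Such a model misses the target by a wide margin.

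**The case against.** The strongest reply is that this rests on silence. The article never says that the vital data are used alone or that the analyses are unadjusted. The quartile comparison is only an example, and covariate lists usually belong in a statistical analysis plan, which is not shown. This stands in part: a missing covariate list would not be a point by itself. But the article goes further than silence. It names the inputs of the regression, itemises those of the combined model, and every one is a sensor feature.

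Other replies also hold, and limit the point:

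- A reader might infer that the associations are confounded. The documents show only a risk of unknown size; with weak links it is negligible.
- A reader might infer that the added value of sensing cannot be shown. It can, because the necessary background data are collected. The analyses described just do not show it.
- A reader might infer that a pitch model that merely detects sex would count as success. Step 4 shows that it would fail the stated RMSE target.
- Confounding does not invalidate a purely predictive model, and the article claims neither a causal effect nor added value over background data. The adjustment matters for Objective 1; the nested comparison matters for interpreting the models.
- The Exclusion Criteria remove people under treatment for mental illness and those with heart disease affecting pulse-wave measurement. This takes away some medication confounding, but leaves age, sex, job and other prescriptions.
- Past stress-check data depend on consent and may be incomplete. The documents also give no basis for saying that employers already hold them.

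**Conclusion.** The point holds in a limited form. As described, the secondary regressions and the machine-learning models have sensor features as their only named inputs, and the background data have no stated analytic role. The Objective 1 associations may therefore partly reflect age, sex or medication, and the described analyses do not separate what sensing contributes from what background data already provide.

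The size cannot be derived from the documents. Over the assumed correlations the spurious r runs from about 0.01 to 0.18, with about 5% to 72% declared significant at n = 200, and a sensor R² of 0.09 may add anything from 0.09 to almost nothing over background. The arithmetic is sound, but the correlations, the 5% level and the PSS standard deviation are all assumptions. The change is worth making because it is cheap, bears directly on Objective 1, and is best settled before models are tuned.

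**What to change.** **Secondary Analysis.** Report each association unadjusted and, beside it, adjusted for at least age, sex and prescriptions relevant to the measured signals. Adjust for company only if the number of companies, which the article does not give, allows it.

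**Tertiary Analysis.** On the same cross-validation folds, report a mean-only model, a background-only model (age, sex, job) and a background-plus-vital-data model. Keep the sensor-only models already planned. Give the change in RMSE from background-only to background-plus-vital-data as the measure of what sensing adds.

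**Past stress-check data.** Use these only for a sensitivity benchmark among participants who consented to their use.

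**Cost.** A few degrees of freedom, a little more analysis work, and possibly less favourable sensor results. No new data are needed, and the target of 300 does not change.
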